**Table 1: Schedule of Visits and Assessments**

**Assessment schedule can vary plus or minus five days for operational convenience**

| Visit                                       | 0
Screening
Phase | 1
Baseline | 2 | 3 | 4 | 5 | 6 | 7 | 8 | 9 | 10 | 11 | 12 | 13 | 14 |
|---------------------------------------------|-------------------------|---------------|---|---|---|---|---|---|---|---|----|----|----|----|----|
| WEEK                                 |                         | 0             | 1 | 2 | 3 | 4 | 5 | 6 | 7 | 8 | 9  | 10 | 11 | 12 | 14 |
| Study medication period(12 weeks)    |                         |               |   |   |   |   |   |   |   |   |    |    |    |    |    |
| SCREENING AND CONSENT                |                         |               |   |   |   |   |   |   |   |   |    |    |    |    |    |
| Assessment of current medication            | X                       |               |   |   |   |   |   |   |   |   |    |    |    |    |    |
| Informed consent                            | X                       |               |   |   |   |   |   |   |   |   |    |    |    |    |    |
| Ongoing capacity                            |                         | X             | X | X | X | X | X | X | X | X | X  | X  | X  | X  |    |
| Inclusion / exclusion criteria              | X                       |               |   |   |   |   |   |   |   |   |    |    |    |    |    |
| Urine pregnancy test (females only)         | X                       |               |   |   |   |   |   |   |   |   |    |    |    |    |    |
| Drug dispensation (after randomisation)     |                         | X             |   | X |   | X |   | X |   | X |    | X  |    |    |    |
| SAFETY                               |                         |               |   |   |   |   |   |   |   |   |    |    |    |    |    |
| Adverse events                              |                         |               |   | X | X | X | X | X | X | X | X  | X  | X  | X  | X  |
| Physical health and metabolic measures      |                         | X             |   | X |   | X |   | X |   | X |    | X  |    | X  |    |
| EFFICACY                             |                         |               |   |   |   |   |   |   |   |   |    |    |    |    |    |
| PANSS TOTAL SCORE                           | X                       | X             |   | X |   | X |   | X |   | X |    | X  |    | X  |    |

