## 7.5 Randomisation Procedure

Participants will be randomised once written consent has been obtained and the baseline assessments have been completed. Participants will be randomised to one of the treatment groups, using blocks of 4 via a computer-generated randomization table. Randomisation will be stratified by five sites (a) Metro North HHS, (b) Metro South HHS, (c) West Moreton HHS, (d) Gold Coast HHS, and (e) Children's Health Queensland HHS. Participants will receive either active treatment or placebo in a 1:1 ratio.

The investigational products will be manufactured in accordance with current Good Manufacturing Practice (GMP) in a suitable TGA licensed facility. This same company (Pharmaceutical Packing Professionals) will hold the randomisation code, and provide a 24 hour

1800 number to unblind participants if required. Participants will be randomised strictly using a chronological process. Participants will be allocated a unique identification number which will be linked to the specific site number. If a participant withdraws from the study then the participant number will not be re-used nor will the participant be allowed to re-enter the study.

The randomisation will be double-blind. An independent Biostatistician will generate the randomisation list which will be provided to the manufacturer. The independent manufacturer will hold the closed randomisation list and be the only one who has the ability to unblind. In the case of emergency where it is crucial the medical staff knows whether the participant is on sodium benzoate or placebo, participants will be provided with contact information (i.e. 24 hour 1800 number) for unblinding.

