## **11 Data Analysis and Statistical Considerations**

### **11.1 Hypotheses**

Those participants allocated to the active arm (1000mg (500mg BD)) Sodium Benzoate treatment will have significant reductions in PANSS total score at week 12 compared to individuals taking placebo.

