### **11.3 Sample Size and Power**

The Lane *et al* study was based on  $n = 52$  patients with chronic schizophrenia. They reported a Cohen's effect size ( $d$ ) of 1.53. Our patients (early psychosis) tend have slightly lower mean PANSS total scores (65.0), with a standard deviation of 14.3 units and it is anticipated that the effect size will be smaller in this group. With an alpha value of 0.05, and power of 0.8, we wish to be able to confidently detect a difference in mean PANSS Total of at least 7 units. This will require 66 participants per group ( $n = 132$ ). Over a 12 week period we predict attrition of 15%. Thus, we will need to randomize approximately 160 subjects.

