### **11.4 Statistical Analysis**

All data will be analysed using SAS 9.4. We will compare demographic and clinical differences between the groups at baseline (Fisher exact test for nominal variables and Mann-Whitney test or independent sample  $t$  test for continuous variables). Efficacy will be assessed according to standard Intention to Treat (ITT) analytic procedures (i.e. for those who do not complete the 12 week study period, we will carry forward their last observation on the study outcomes). Mean changes in clinical assessment will be assessed using mixed-model repeated-measure (MMRM) methods with treatment, week, and treatment-week interaction as fixed effects and intercept as the only random effect; baseline value will be the covariant. The MMRM analyses will be performed using the SAS PROC Mixed procedure.  $P$  values will be based on 2-tailored tests with significance levels of 0.05.

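### Section 11.4 gives baseline PANSS one slope for all six visits although the hypothesis is about week 12; a baseline-by-week term would be a cheap, optional gain in precision

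*Protocol*

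**What the plan says.** Section 11.4 describes a mixed model for repeated measures with "treatment, week, and treatment-week interaction as fixed effects and intercept as the only random effect; baseline value will be the covariant". Baseline appears once. No interaction of baseline with week is named, and none is ruled out.

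Section 11.1 states the hypothesis at a single visit: the active arm "will have significant reductions in PANSS total score at week 12 compared to individuals taking placebo". In Table 1 the row "PANSS TOTAL SCORE" is marked at weeks 2, 4, 6, 8, 10 and 12 after baseline, so six post-baseline visits feed the model. Section 11.4 also carries the last observation forward for participants who do not complete the 12 weeks.

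Section 11.3 sizes the trial to "detect a difference in mean PANSS Total of at least 7 units", "with a standard deviation of 14.3 units". It mentions no correlation between baseline and outcome.

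**The concern.** With baseline entered only as a main effect, the model assumes that baseline PANSS predicts week 12 exactly as strongly as it predicts week 2. If that association fades over the visits, the common slope is steeper than the slope appropriate to week 12. The week-12 difference is then over-corrected for whatever chance imbalance the arms show at baseline, and its variance is larger than it need be.

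What is at stake is some precision at the one visit named in the hypothesis, for the sake of a constancy assumption that the protocol neither states nor justifies.

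**Working it through.** **The plan's own figure.** The inputs from Sections 11.3, 11.4 and 7.5 are:

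- "With an alpha value of 0.05, and power of 0.8"
- two-sided testing ("values will be based on 2-tailored tests with significance levels of 0.05")
- difference 7, SD 14.3
- equal allocation ("Participants will receive either active treatment or placebo in a 1:1 ratio")

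The normal-approximation sample size is n per arm = 2 × (1.960 + 0.842)² × 14.3² / 7² ≈ 65.5, rounded up to 66, or 132 in total. Power at 66 per arm is 80.3%. Inflating for 15% attrition gives 132 / 0.85 = 155.3, or 156 as an even total, which is consistent with the plan's approximately 160. The figure reproduces, and it uses the raw SD with no reduction for baseline adjustment.

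**Assumptions for the check.** The documents give no correlations between baseline and later visits, so these are assumed over a range. SDs are taken as equal at all visits. The data are treated as complete, which carrying observations forward approximates.

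**Formulas.** Let ρ₁₂ be the correlation of baseline with week 12. With balanced data and a random intercept only, the common slope b is the mean of the six visit slopes. In units of the raw variance, the week-12 contrast then has

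- variance with the common slope: 1 − 2bρ₁₂ + b²
- variance with a week-specific slope: 1 − ρ₁₂²
- excess: (b − ρ₁₂)², which is zero or positive.

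Worked case, correlation falling linearly from 0.80 at week 2 to 0.50 at week 12:

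- b = 0.65
- common slope: 1 − 2 × 0.65 × 0.50 + 0.65² = 0.7725
- week-specific slope: 1 − 0.50² = 0.75
- ratio 1.030.

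| Assumed correlation, week 2 to week 12 | b | ρ₁₂ | Variance ratio | Power at 66 per arm, common vs week-specific |
|---|---|---|---|---|
| flat 0.50 | 0.500 | 0.500 | 1.000 | 90.1% vs 90.1% |
| 0.75 to 0.60 | 0.675 | 0.600 | 1.009 | not computed |
| 0.70 to 0.50 | 0.600 | 0.500 | 1.013 | 89.7% vs 90.1% |
| autoregressive, 0.95 per two weeks | 0.839 | 0.735 | 1.023 | 98.4% vs 98.6% |
| 0.80 to 0.50 | 0.650 | 0.500 | 1.030 | 89.2% vs 90.1% |
| 0.80 to 0.45 | 0.625 | 0.450 | 1.038 | not computed |
| autoregressive, 0.90 per two weeks | 0.703 | 0.531 | 1.041 | 90.2% vs 91.3% |
| autoregressive, 0.80 per two weeks | 0.492 | 0.262 | 1.057 | 80.9% vs 83.0% |
| 0.85 to 0.40 | 0.625 | 0.400 | 1.060 | 84.6% vs 86.6% |
| 0.85 to 0.30 (extreme) | 0.575 | 0.300 | 1.083 | not computed |
| 0.90 to 0.30 (extreme) | 0.600 | 0.300 | 1.099 | 80.3% vs 83.8% |

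**Where planned power would be at risk.** The common-slope variance exceeds the unadjusted variance only if b > 2ρ₁₂. The most extreme row, 0.90 to 0.30, sits exactly on that boundary (0.60 = 2 × 0.30) and gives back the planned 80.3%. Every other row lies inside it.

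**Simulation check.** The three autoregressive patterns were simulated with 66 per arm, 4,000 replicates each and a true week-12 difference of −7. Mean estimates were −6.98 to −7.00 under both models, so neither slope choice biases the contrast. The SDs of the estimate, common vs week-specific, were:

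- 0.95 per two weeks: 1.726 vs 1.707, squared ratio 1.022
- 0.90 per two weeks: 2.148 vs 2.103, squared ratio 1.043
- 0.80 per two weeks: 2.456 vs 2.386, squared ratio 1.060.

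The formula gives 1.023, 1.041 and 1.057.

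**The same loss seen conditionally.** With 80 per arm, the chance baseline difference has variance 14.3² × 2/80 = 5.112. Its 95% limit is 1.96 × √5.112 = 4.43 points. At that limit, the estimate under 0.80 to 0.45 moves by (0.625 − 0.45) × 4.43 = 0.78 points. Across the patterns 0.75 to 0.60 and 0.85 to 0.30, the move is 0.33 to 1.22 points. For 0.80 to 0.45, the variance of this shift over randomisations is 0.175² × 5.112 = 0.157. The week-specific contrast variance is 5.112 × 0.7975 = 4.077, and 0.157 / 4.077 = 3.8%. That is the excess already in the table.

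**The case against.** The strongest case against raising this is that a single baseline slope is a conventional and valid specification. Nothing in the documents shows that the association weakens; if it is flat, nothing is lost. Carrying early scores forward raises the apparent correlation of week 12 with baseline and so may soften any decay. Even with decay, the cost is a few percent of variance on assumed correlations, with planned power intact. Baseline-by-week terms are also typical detail for an analysis plan, which is not shown here and may already include one.

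Most of this stands. It makes the point conditional and small. It does not remove it, because Section 11.4 does not leave the mean model open: it writes the fixed effects out, and the hypothesis rests on the last visit. Apart from a few degrees of freedom, the model as written can only match or lose to the one with week-specific slopes. If the analysis plan already adds the term, nothing further is needed.

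Four stronger readings are tempting and are not supported:

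- **That the week-12 estimate is biased, or adjusted with a slope known to be wrong.** The documents contain no correlations from which to say so, and over randomisations the slope choice introduces no bias.
- **That the shift under chance baseline imbalance is a further harm.** It is the same variance excess, viewed for one realised imbalance.
- **That the loss is larger because an unstructured covariance would make it so.** Section 11.4 specifies a random intercept only, so figures for another covariance do not describe this plan.
- **That leaving out the screening PANSS is an error.** Table 1 does record PANSS at both screening and baseline, and Section 7.5 places randomisation after the baseline assessments. But adjusting for one labelled baseline is standard. The screening score serves the eligibility threshold of 55 in Section 4.2, and its added value depends on correlations that the protocol does not give. Under purely autoregressive decay it would add nothing once baseline is in the model.

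**Conclusion.** The point holds as an optional efficiency refinement. As written, the model forces one baseline slope on six visits while the hypothesis concerns only the last. The cost in week-12 variance is zero under a flat association, about 1-6% under plausible decay and about 8-10% under extreme decay. All of these figures rest on assumed correlations, equal SDs over visits and near-complete data.

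Power remains at or above the planned level in every pattern for which it was computed. These power figures use the actual variance of the contrast. Whether the random-intercept model reports that variance correctly, and what carrying observations forward does to the estimate, are separate questions not settled here.

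**What to change.** In Section 11.4, or in the statistical analysis plan, add a baseline-by-week interaction to the fixed effects, declare week as a class variable, and state that the week-12 treatment difference is taken from that model. Do this before unblinding, so that the choice cannot look data-driven.

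The cost is one line of wording and one further term in PROC MIXED. With six post-baseline visits the interaction uses five extra degrees of freedom among approximately 160 participants. It needs no new data and no change to the sample size.

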## **12 Data Management**

### **12.1 Documentation**

A screening log will be utilized to track potential participants and also record the counts of individuals approached, consented, meeting inclusion/exclusion criteria, withdrawals, and completion (in keeping with standard CONSORT diagram requirements).

The Case Report Form (CRF) will comprise of the hard copy questionnaires, clinical assessments and measures. These de-identified data will be retained in a secure room, in a locked filing cabinet, at each site.

De-identified data from the CRFs will be entered into REDCap, which is a secure (encrypted to health service standard, housed on a server behind the University of Queensland firewall), web-based application for building and managing online surveys and databases. Delegated research assistants will be trained in, and responsible for, entering data into the database.

Upon completion and resolution of monitoring and data management queries, the clinical trial database will be closed. All data will be exported into SAS software to enable statistical analysis.

A copy of the PICF will be stored in a secure room in a locked filing cabinet separate from the CRFs.

### **12.2 Archiving**

The Investigator, Project Manager or their delegate at each site will organise the retention of documentation relating to the study (source documents, informed consent forms, approvals) for a period of at least 15 years or the maximum time frame as determined by local regulations, whichever is the longest.

## **13 Monitoring and Quality Assurance**

An independent Study Monitor will conduct study documentation review to monitor key features of the study prior to commencement, during and after study completion. These site visits will enable the Monitor to maintain current, personal knowledge of the study through review of the CRFs, comparison of CRF entries against the electronic data base (REDCap) and discuss the conduct of the study with the Investigator. The Monitor will be responsible for monitoring adherence to the approved study protocol, regulatory compliance including GCP and completion of the CRF. The organisation, supply of study materials and quality assurance of the clinical trial is the responsibility of the Investigator or its designee.

In order to ensure the accuracy of data, direct access to source documents by the representatives of both the Study Monitor and regulatory authorities will be available.

The Investigator will submit to the Reviewing HREC, annual (or more frequent if requested) reports of the study.

The study coordinator or designated delegate will monitor data entered at each site and be responsible for resolving data entry errors and discrepancies.

Data quality will be ensured by performing data entry checks for consistency between the CRF and the data entry into REDCap database. These checks will be performed during data entry so that discrepancies can be resolved immediately. A data manager will later perform additional checks for completeness and plausibility of data. Resultant queries will be raised and resolved electronically by the data manager and the study centre.

Each site will maintain a record of all personnel involved in the study including a Signature & Delegation Log which the Investigators will sign. In consultation with the lead site, each site will ensure that appropriate training is provided to study personnel, and that any new information of relevance to the performance of this study is forwarded to the staff involved in a timely manner.

### **13.1 Data Safety Monitoring Board**

An independent Data Safety Monitoring Board (DSMB) will be established specifically to monitor safety data and study trends throughout the duration of the trial to determine if continuation of the trial is appropriate scientifically and ethically. The members of the DSMB serve in an independent capacity and will provide their expertise and recommendations to guide the clinical trial where required.

## **14 Investigator Responsibility**

Except where the Coordinating Principal Investigator's signature is specifically required, it is understood that the term 'Investigator' as used in this Protocol and on the CRFs refers to the Coordinating Principal Investigator and the Principal Investigator or an appropriately qualified member of the staff that the Coordinating Principal Investigator designates to conduct the study. The Coordinating Principal Investigator is ultimately responsible for the conduct of all aspects of the study.

The study and its associated documents will be reviewed and approved by the appointed certified HREC and Research Governance (at all sites) before study start. A signed and dated letter that the ethics application has been approved by the appointed HREC and Research Governance Authority will be provided to the Sponsor before study initiation.

Prior to submission to appointed HREC and Research Governance, the investigator will sign the protocol signature page confirming his/her agreement to conduct the study in accordance with the protocol, GCP and other regulatory requirements locally applicable. All relevant data and records will be provided to study monitors, HREC and regulatory authorities as required. If an inspection of the clinical site is requested by a regulator, the investigator will inform the University of Queensland (Sponsor) immediately that this request has been received.

Each Investigator will comply with the local regulations regarding clinical trials and the Investigator responsibilities outlined in the ICH GCP guidelines.

## **15 Study Report**

The Investigator will submit at least annual study reports to the reviewing HREC, or more frequent if needed.

## **16 Administrative Procedures**

### **16.1 Ethical Considerations**

Information on side effects of the Investigational Product and reference formulations is summarised in the Investigator's Brochure. The monitoring and safety guidelines are outlined in the Monitoring Guidelines for the study. This study will be carried out according to the Declaration of Helsinki, the NHMRC National Statement on Ethical Conduct in Research Involving Humans (2007) and the Notes for Guidance on Good Clinical Practice as adopted by the Australian Therapeutic Goods Administration (2000) (CPMP/ICH/135/95) and the ICH GCP Guidelines.

### **16.2 Ethical Review Committee**

The National Ethics Application Form (NEAF) and associated documents will be submitted for approval to the appointed multi-site HREC and written approval obtained from both the appointed HREC and Governance Office, before volunteers are recruited and participants are enrolled. The Chief Investigator will submit the National Ethics Application Form and associated documents including Site Specific Applications from each site, to the appointed HREC and Research Governance. The Chief Investigator has overall responsibility to ensure all reports at each site are submitted in line with the appointed HREC reporting requirements.

### **16.3 Regulatory Authorities**

The study will be notified under the Clinical Trial Notification (CTN) scheme. The University of Queensland (Sponsor) will submit the CTN forms from each participating site. The trial will also be listed on the Australian and New Zealand Clinical Trials Registry.

In agreeing to the provisions of the Protocol, these responsibilities are accepted by the Investigators.

### **16.4 Informed Consent**

Our criteria will ensure that recruited participants will be sufficiently competent to consent and participate in the study or to refuse consent. Current research provides evidence that while psychotic symptoms may be present, these do not robustly predict an individual's functionality in daily life and capacity to make decisions, and whilst strongly correlated with cognitive impairment, do not reflect an enduring inability to understand information related to research participation.

#### **16.4.1 Adult participants (18-45 years inclusive)**

Eligible adult participants (18-45 years) will be given a full explanation in lay terms, with a friend or family member present if desired, of the study aims, the discomfort, risks and benefits in taking part and a copy of the Participant Information Sheet Consent Form to review.

It will be pointed out to adult participants that they can withdraw from the study at any time without prejudice and will not affect their current care. The adult participants will have the opportunity to ask questions. A telephone number will be provided so that adult participants can call a research representative who will be able to respond to any questions they may have.

Each adult participant will acknowledge receipt of this information by giving written informed consent for participation in the study. The consent form will be signed and dated by a witness. A notation that written informed consent has been obtained will be made on the participant's Case

report Form (CRF). The original, completed consent forms will be retained by the Investigator and a copy will be provided by the research staff to the participants.

